### Intervention description {11a}

Percutaneous pinning CRPP:Preparation: Once the fracture is reduced, percutaneous pinning involves the insertion of two metal pins (also known as Kirschner wires or K-wires) into the bone to maintain alignment and stability during the healing process.Selection of pins: The surgeon selects appropriate-sized K-wires based on the patient’s age, bone size, and fracture characteristics. These pins are typically made of stainless steel or titanium and come in various diameters and lengths.Insertion: Using a percutaneous approach (through the skin), the surgeon carefully inserts the K-wires across the fracture site and into the bone under fluoroscopic guidance to ensure accurate placement. The pins are driven through the skin and soft tissues and into the bone fragments.Configuration: Depending on the fracture’s complexity and stability, the pins may be placed in different configurations (such as crossed from both sides or parallel from the radial side) to provide optimal stability and alignment.Safe pin insertion: a pin introduced from the medial side passes close to the ulnar nerve and a small open wound is required to ensure that the nerve is not injured in this process.Confirmation: Once the pins are in place, the surgeon verifies their position and alignment using imaging techniques, such as X-rays, to ensure proper fixation of the fracture fragments.After completing the closed reduction and percutaneous pinning, the surgical site is typically dressed, and the patient is monitored in the recovery room before being transferred to a hospital ward for further observation. Postoperative care may involve immobilisation of the elbow using a splint or cast, pain management, physical therapy, and follow-up appointments to monitor healing progress and remove the pins at 3 to 4 weeks. The goal of CRPP is to restore normal alignment and function of the elbow joint while promoting optimal healing and minimising the risk of complications.

Lateral straight arm traction LSATThe child should be placed in straight arm traction as soon as the diagnosis and treatment plan have been made.Consent may be taken verbally from a parent or guardian.The child is given a strong but appropriate dose of analgesia or sedation from a trained practitioner.Skin traction is applied to the forearm of the injured arm from the level of the elbow crease to the wrist crease. If necessary, a crepe bandage may be applied around the forearm from distal to the elbow crease to help the skin traction to stick. However, any such bandage must NOT be bound in any tension and must be removed if the child complains of pain or that it is tight or if there are concerns about the circulation or compartments.The traction cord extending from the skin traction beyond the hand is tied to a drip stand.The drip stand is placed beside the bed so that the angle of the axilla is 90°.The elevation of the drip stand is adjusted so that the child’s arm is elevated off the bed with the elbow almost straight. An angle of 30 to 60° should be present between the mattress and the elevated arm.The elbow should not be flexed more than 30°.The child is given regular oral analgesia (preferably paracetamol and ibuprofen at appropriate doses) for the first 5 days or until comfortable.The traction is checked daily for circulation and movement (rock/paper/scissor/ok); and for slippage or blistering on the skin.Traction may be applied by any appropriate member of the T&O team. However, the traction set up must be checked by a consultant T&O surgeon within 24 h of application, or sooner if there are any problems.If there are any concerns regarding compartment syndrome or impaired circulation to the hand, then all circumferential bandages or dressings must be removed immediately, and the surgeon informed immediately.The traction should be kept there for at least 5 days, and the child should be assessed for comfort. If the swelling has all receded and the child is comfortable to flex the elbow to at least 90°, then a posterior slab should be applied with the forearm in mid prone and the elbow flexed at least 90°. Radiographs of the affected elbow AP and lateral will be taken in the cast, and if satisfactory, the child will be allowed home to attend for cast removal at 4 weeks from injury.If at least 5 days of the traction, if there is still swelling or the child has too much pain to flex the elbow to 90°, then straight arm traction should be continued until such a time as this becomes possible.If a child reaches 4 weeks in traction without qualifying for conversion to a backslap, then a fresh radiograph should be taken. If the problem is stiffness but pain is controlled and callous is present, the child can be released from traction and taught to bend the elbow, and allowed home with no backslap. No traction or back slab should be retained for more than 4 weeks since the injury.If at 4 weeks, there is still pain and swelling and little callous, then the surgeon must assess the situation to decide on whether to prolong traction or switch to surgical management.

### Criteria for discontinuing or modifying allocated interventions {11b}

The study design is pragmatic, and treating surgeons are permitted to intervene according to their clinical expertise and judgement. Cross-over is much more likely to occur from the non-operative LSAT to the operative CRPP, although in theory, a CRPP could be put in traction after surgery.

All cross over patients must be recorded as such, and the reasons for cross over recorded.

Likely reasons for crossover from LSAT to CRPP would be patient or guardian intolerance; skin reaction to traction material; failure to control pain; arterial or nerve compromise deemed to require surgical intervention.

### Strategies to improve adherence to interventions {11c}

Adherence will be more of an issue with the LSAT arm of the study, which has the potential to cross over.

The surgeons have been educated in application and expectations for this technique. The site PIs are also educating their colleagues and the nurses in their institutions regarding LSAT.

The patient information, counselling and consent is key to helping the children and their guardians understand what is being offered and undertaken on their behalf.

### Relevant concomitant care permitted or prohibited during the trial {11 d}

The trial is pragmatic and surgeons are able to use their clinical judgement to deliver the best possible care in the interests of the children.

One anticipated non-adherence is that in the operative CRPP group, some surgeries will end up being performed using open reduction. This may happen because closed reduction cannot be achieved, or because the C arm required for assessment of closed reduction is not available or not working. Such cases will remain in the study under the CRPP arm as randomised.

### Provisions for post-trial care {30}

The care of all patients is within the public health system of Ethiopia. Any ongoing care needs will continue to be incorporated into that health system.

### Outcomes {12}

Primary outcome: PROMIS Parent Proxy Upper Extremity – short Form 8a version 3.0, administered to patient guardian at 12 months after injury by an independent technician using Amharic or appropriate language explanation over telephone. The technician scorer will be blinded to the type of treatment received by the child and will not be permitted to ask which treatment was received.

Secondary outcomes:PROMIS Parent proxy Upper Extremity – short form 8a v3.0 at 6 monthsPROMIS Parent Proxy Global Health 7 + 2 v3.0 score at each of 6 and 12 monthsComplications, notably nerve injury, arterial compromise, Volkmann contracture, infection, secondary intervention. Scored by surgeon assessors at 3 months post injury by face-to-face clinical review.Flynn’s criteria for elbow range of movement and carrying angle assessed clinically in person by treating surgeons at 3 months after injury.Patient satisfaction with treatment using 10-point visual analogue scale. Scored in person by patient guardian, administered by treating surgeon at 3 months after injury.Economic analysis of hospital costs. Time and motion study at two representative hospital sites assessing both LSAT and CRPP using median hospital stays.

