Traction is well documented to result in a longer hospital stay than operative intervention. Duration of inpatient stay was in the range of 11–22 days with a median of 19 days. Two papers used length of stay as contributing factors to their cost analysis, both concluding traction was considerably more expensive than pinning [17, 25]. When considering duration of stay, theatre fees, anaesthetic fees, recovery room fees, and radiography fees, Sutton et al. and Piretto et al. calculated traction was more expensive by 142% and 179%, respectively. However, both papers were based in high-income countries, where costs of both equipment and service provision make calculations non-transferable to less economically developed nations. The use of traction for Gartland types II and III supracondylar fractures provides a safe and effective alternative to percutaneous wire fixation in the resource-poor setting. In countries where few specialist centres are managing increasingly high volumes of trauma, the benefit of such surgical intervention remains to be proven. With the correct expertise, traction can be safely applied in a local setting, avoiding the need for long-distance transfer and associated financial cost.

Currently there is no Level-1 evidence comparing percutaneous pin fixation with traction for displaced supracondylar fractures of the distal humerus in children. Drawing on conclusions from the studies reviewed, there is a suggestion that these two management options remain part of the solution with no clear recommendation.

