### Objectives {7}

To test if LSAT is non inferior to CRPP as measured by the PROMPROMIS Parent Proxy Upper Extremity – Short Form 8av3.0 at 12 months after injury, and in the LMIC context.To assess Global Health at 6 and 12 months using PROMISParent Proxy Global Health 7+2 v3.0To assess complications of both LSAT and CRPPEconomic evaluation to compare hospital-based costs for LSAT and CRPPTo compare elbow function by Flynn’s criteria 3 months after LSAT/CRPP To compare guardian satisfaction with treatment by LSAT/CRPP 

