## Interventions

### Explanation for the choice of comparators {6b}

The two treatment modalities chosen are accepted in the literature to give excellent results, and if delivered correctly, can give a low rate of complications.

Lateral straight arm traction LSAT is a low-cost intervention which can be administered by trained orthopaedic technicians. It avoids surgery or anaesthesia but has a longer length of hospital stay.

Closed reduction and percutaneous pinning CRPP is the most popular treatment method in High Income Countries HICs. It requires an operation under general anaesthetic, with a trained T&O surgeon, and availability of a C-arm for radiographic imaging during the operation. It allows a shorter average hospital stay, with the child normally discharged from hospital within 48 h of surgery (Table 1).

**Table 1 Tab1:** Schedule of enrolment interventions and assessment

	Study period						
	Enrolment	Allocation	Post allocation				Close-out
Timepoint			Within 48 h	4 weeks	3 months	6 months	12 months
Enrolment	X						
Eligibility screen	X						
Informed consent	X						
Allocation		X					
Interventions							
Closed reduction and perc pinning			X				
Lateral straight arm traction			X				
Assessments							
Flynn’s criteria				X	X		
Complications				X	X		
PROMIS scores						X	X

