### Participant timeline {13}

Arrive at hospital within 72 h of injury.

Invitation to join study and informed consent process.

Treatment administered within 48 h of consent.

Discharge in plaster backslab when clinically safe as judged by treating surgeons. Minimum time for LSAT is 5 days.

Clinical outpatient review 4 weeks after injury to remove plaster and start self-mobilisation.

Clinical review 3 months after injury and discharge from clinical reviews if outcome judged satisfactory by treating surgeons.

Telephone review 6 and 12 months after injury.

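### The hospital-cost comparison is based on median stays, which do not estimate cost per child when stays are skewed; an understated LSAT cost is plausible but not certain

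*Protocol article*

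**What the plan says.** Objectives {7} lists an economic "evaluation to compare hospital-based costs for LSAT" and CRPP. Outcomes {12} makes this a secondary outcome and names the method: "Time and motion study at two representative hospital sites assessing both LSAT and CRPP using median hospital stays". No other section promises mean or patient-level costs.

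Four further statements bear on the shape of the stays:

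- Participant timeline {13}: "Minimum time for LSAT is 5 days".
- Intervention description {11a}: if swelling or pain still prevents flexion after that minimum, "then straight arm traction should be continued until such a time as this becomes possible".
- The same section sets a limit, "No traction or back slab should be retained for more than 4 weeks since the injury", but goes on to say that if pain and swelling persist with little callus at 4 weeks, "then the surgeon must assess the situation to decide on whether to prolong traction or switch to surgical management".
- Explanation for the choice of comparators {6b} describes CRPP "with the child normally discharged from hospital within 48 h of surgery".

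On earlier traction series, the Literature review says: "Duration of inpatient stay was in the range of 11–22 days with a median of 19 days".

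**The concern.** The economic question is what each treatment costs the hospital per child. A hospital pays for every bed-day, including those of the children who stay longest. The median does not move however long the longest stays become, so a costing built on it can leave out days that are actually paid for.

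The summary measure is written into the protocol, so this is a stated choice and not a detail left to an analysis plan. It matters because affordability is part of the trial's case: the abstract's Discussion says that a non-inferior LSAT would allow cost-effective local treatment, and the Literature review reports long stays and their cost as the historical reason for moving away from traction. The non-inferiority conclusion on the primary outcome is not affected.

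**Working it through.** The protocol states no cost, mean stay or spread of stay, so there is no figure of its own to reproduce.

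**Step 1: which summary gives cost.** With n children, stays L₁ … Lₙ and a cost c per bed-day, total bed-day cost = c × ΣLᵢ = c × n × mean(L). Cost per child is therefore c × mean(L), whatever the distribution. c × median(L) equals it only if mean and median coincide. This step needs no assumption about shape.

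**Step 2: direction in the LSAT arm.** Inputs from the protocol: a floor of 5 days, continuation until criteria are met, a 4-week limit counted from injury, and possible prolongation beyond it. A floor with a possible tail of weeks makes mean > median plausible. A floor alone does not fix the skew.

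**Step 3: illustrative size (assumed distribution).** Let stay = 5 + 3·exp(s·Z), with Z standard normal. The median is 5 + 3 = 8 days. Uncapped, the mean is 5 + 3·exp(s²/2). To respect the 4-week limit, cap stay at 28 days, that is, cap the excess at 23 days. With d = ln(23/3)/s, the capped mean is 5 + 3·exp(s²/2)·Φ(d − s) + 23·(1 − Φ(d)). The understatement is 1 − 8/mean.

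| Log-SD s | Mean, uncapped | Understated | Mean, capped at 28 | Understated |
|---|---|---|---|---|
| 0.5 | 8.40 | 5% | 8.40 | 5% |
| 1.0 | 9.95 | 20% | 9.68 | 17% |
| 1.25 | 11.55 | 31% | 10.43 | 23% |

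At s = 1.25 the uncapped model puts about 5% of children past 28 days, and the 31% depends on them.

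**Step 4: other assumed medians, capped at 28 days, log-SD 0.5 to 1.2 (simulation).**

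| Median stay | Mean stay | Gap in days |
|---|---|---|
| 7 | 7.3 to 8.8 | 0.3 to 1.8 |
| 10 | 10.7 to 12.8 | 0.7 to 2.8 |
| 14 | 15.0 to 16.2 | 1.0 to 2.2 |
| 19 | 19.0 to 19.6 | 0 to 0.6 |

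**Step 5: checks that could go the other way.**

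- *Cited traction stays.* A shape with half the stays uniform on 11–19 days and half on 19–22 has mean 0.5 × 15 + 0.5 × 20.5 = 17.75, below the median of 19. Here the median would overstate.
- *CRPP arm.* With an assumed log-normal stay of median 1 or 2 days and log-SD 0.5 to 1.0, mean minus median is median × (exp(s²/2) − 1), or 0.13 to 1.30 days. The LSAT gap in Step 3 (capped) is 0.40 to 2.43 days. It is usually the larger, but not in every pairing: 0.40 for LSAT at s = 0.5 is less than 1.30 for CRPP at median 2 and s = 1.0.
- *Early crossover.* With log-SD 0.8 and a cap at 28 days, median and mean are 8.0 and 9.1. If 10% or 20% of LSAT children leave traction early with stays of 1 to 4 days, they become 7.7 and 8.4, or 7.3 and 7.8. The gap shrinks but does not reverse.

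**The case against.** The strongest reply accepts Step 1 and disputes direction and size. Most of it stands.

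- **Tail.** The LSAT tail is not simply open. The 4-week limit and the later allowance to prolong traction are in tension and must be reconciled. If the limit binds, the gap shrinks.
- **Evidence on shape.** The only traction stays in the document do not look right-skewed. They may be study-level figures from other settings, so they do not prove the opposite, but they give no support for assuming a long right tail.
- **CRPP arm.** The 48 h runs from surgery, not admission, and is only the normal case. Waiting for theatre and conversion to open reduction can lengthen CRPP stays. In relative terms the CRPP error could be the larger: at log-SD 1.0 a log-normal CRPP stay is understated by 1 − exp(−0.5) = 39%, against 17% for the capped LSAT model.
- **Costing formula.** The article does not say how the time-and-motion results and the median stays are combined.

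Three stronger readings are tempting, and the documents support none of them. A reader might infer that stay is the main cost driver for traction; the Literature review calls it one contributing factor, alongside theatre, anaesthetic, recovery-room and radiography fees, and regards those high-income costings as non-transferable. A reader might infer that the trial could report LSAT as cheaper when it costs the hospital more; that would need bed-day and theatre costs, and none are given. A reader might take the 31% as the likely error; it comes from ignoring the 4-week limit. The absence of a stated interval is not a fault either, since an article may leave that to an analysis plan.

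None of this makes the median the right quantity for cost.

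**Conclusion.** The point holds in a limited form. Median stays do not estimate cost per child or the cost difference between arms when stays are skewed, and the protocol commits to them. This part rests only on costs accruing by bed-day.

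That the error favours LSAT is plausible from the 5-day floor and the continuation rule, but it is not established. The size is unknown. The 5% to 23% understatement of LSAT bed-days is an illustration that assumes a median of 8 days, a log-normal excess over 5 days with log-SD 0.5 to 1.25, and a cap at 28 days. It concerns LSAT bed-days, not the cost difference. The outcome is secondary, and the correction is small and worth making.

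**What to change.** In Outcomes {12}, replace the reference to median stays with: *using the mean of the children's actual hospital stays in each randomised arm*. Report the mean cost difference with a confidence interval, for example by bootstrap. Keep the median and interquartile range of stay as description only.

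The cost is one sentence of text plus extraction of admission and discharge dates from each child's record; the protocol does not state that these are available, so that is an assumption. The mean is more sensitive than the median to a few long stays, so the estimate may be less precise and the LSAT figure may become less favourable. No treatment or visit changes.

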### Participant timeline {13}

Arrive at hospital within 72 h of injury.

Invitation to join study and informed consent process.

Treatment administered within 48 h of consent.

Discharge in plaster backslab when clinically safe as judged by treating surgeons. Minimum time for LSAT is 5 days.

Clinical outpatient review 4 weeks after injury to remove plaster and start self-mobilisation.

Clinical review 3 months after injury and discharge from clinical reviews if outcome judged satisfactory by treating surgeons.

Telephone review 6 and 12 months after injury.

### Sample size {14}

Power analysis has been performed to determine the sample size required for a non-inferiority study based on the PROMIS Upper extremity parent proxy short form 8a version 3.0 score primary outcome, with the Mean Clinically Important Difference MCID set at 3.5 to detect clinically significant differences between the two treatment groups. Initial calculations suggest 202 patients would be required (101 per group). We will aim to recruit 222 patients to the study, leaving a 10% margin of error to account for loss to follow-up. Patients will be randomly assigned to either the straight arm traction group (Group 1) or the operative treatment group (Group 2) using a computer-generated randomisation sequence. Allocation concealment will be maintained to ensure blinding.

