**Methods:**

The study will be a prospective randomised trial comparing lateral straight arm traction LSAT against CRPP. Recruitment will be at 8 large referral hospitals in Ethiopia. Based on non-inferiority power calculation, we plan to recruit 220 patients.

The principal outcome measure will be the PROMIS parent proxy upper extremity short form 8a score version 3.0 at 12 months.

The secondary outcome measures will be the Flynn’s criteria; complications; PROMIS parent proxy upper extremity short form 8a score version 3.0 at 6 months; PROMIS parent proxy global health 7 + 2 score version 3.0 administered at 6 and 12 months; and economic analysis of hospital costs for the two treatment modalities.

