## Assignment of interventions: allocation

### Sequence generation {16a}

Randomisation will be computer generated block randomisation to ensure equal numbers over the intended sample size of 220 patients. Randomisation will be stratified according to the Gartland 2b (rotational displacement only) and Gartland 3 (total off-end displacement) fractures as these are seen to represent separate patient sub-groups.

Ensuring equal numbers of each of these two sub-groups in each treatment arm will eliminate bias based on injury severity characteristics.

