## Statistical methods

### Statistical methods for primary and secondary outcomes {20a}

The data analysis will be conducted by a statistician who is blind to the treatment groups and has not been part of the clinical study.Analyse the primary outcome using appropriate statistical methods, such as linear mixed-effects models or generalised estimating equations, adjusting for baseline functional status and potential confounders. The means of the 12-month PROMIS UE Proxy score will be used for assessing a difference above the MCID. Range analysis, including negative outliers, will also be assessed and presented in the results.Report estimated treatment effects.Compare the incidence of complications between treatment arms using appropriate statistical tests (e.g. chi-square test, Fisher’s exact test).Calculate relative risks or odds ratios for complications between treatment arms with corresponding confidence intervals.Explore potential treatment effect modification by conducting subgroup analyses based on relevant patient characteristics (e.g. age, fracture severity).Evaluate for interaction effects between treatment assignment and subgroup variables.

Missing data handling:Assess the extent of missing data and explore reasons for missingness, particularly for outcome variables.Utilise appropriate methods for handling missing data, such as multiple imputation or sensitivity analyses, to assess the robustness of results.Over-recruit by 10% case numbers above the power calculation to mitigate for missing data.

Sensitivity analyses:Perform sensitivity analyses to examine the impact of different assumptions or analytical approaches on study results (e.g. excluding patients with incomplete follow-up, adjusting for potential confounders).We intend to analyse and present results according to ‘intention to treat’ but will also undertake and present an analysis of ‘actual treatment’.

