### Interim analyses {21b}

Since both treatment options are established and accepted options, and the LSAT method may be slower to achieve full recovery of function and therefore PROM, the study will be allowed to recruit the expected 220 patients unless a safety concern is raised by the PIs or the complication findings. Complication findings will be assessed at 3-month intervals or additionally if a concern is raised.

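### The recruitment target is 222 in one section and 220 in three others; 220 meets neither stated 10% allowance, and 222 tolerates about 9% loss rather than 10%

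*Protocol article*

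**What the plan says.** All references are to the protocol article.

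- **Sample size {14}** puts the requirement at 202 patients, 101 per group, for the 12-month PROMIS upper extremity score, "with the Mean Clinically Important Difference MCID set at 3.5". It then sets the target: "We will aim to recruit 222 patients to the study, leaving a 10% margin of error to account for loss to follow-up".
- **Abstract, Methods**: "Based on non-inferiority power calculation, we plan to recruit 220 patients".
- **Sequence generation {16a}**: block randomisation is used "to ensure equal numbers over the intended sample size of 220 patients".
- **Interim analyses {21b}**: unless a safety concern arises, "the study will be allowed to recruit the expected 220 patients".
- **Statistical methods {20a}**, under missing data: "Over-recruit by 10% case numbers above the power calculation to mitigate for missing data".

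So there are two targets. The allowance of 10% is also described in two ways: once as a margin for children lost to follow-up, and once as a percentage added to the calculated number.

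**The concern.** The target is a core design figure, and the article gives two values for it. The section that derives it says 222. The sections on the randomisation sequence and on how far recruitment may run say 220, and the Abstract presents 220 as resting on the power calculation. A reader cannot tell whether stopping at 220 completes the sample or falls short of it. Recruitment {15} also plans extra centres if the whole sample cannot be recruited in 12 months, so the whole sample should be a single number.

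The two descriptions of the 10% are not equivalent either. Adding 10% to a number and then losing 10% of the total does not return the starting number. The primary outcome is a telephone score at 12 months, so the loss that the sample can absorb matters to anyone judging follow-up.

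**Working it through.** **Inputs.** Required analysable number 202 (Sample size {14}). Targets 222 (Sample size {14}) and 220 (Abstract; Sequence generation {16a}; Interim analyses {21b}). Allowance 10%, worded as loss to follow-up in {14} and as over-recruitment in {20a}. The SD, alpha and power are not stated, and steps 1 to 4 do not need them.

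**Step 1. Reproduce the plan's own figure.** Over-recruitment by 10% is 202 × 1.10 = 222.2, which gives 222. The figure in Sample size {14} therefore follows the rule in {20a}. No stated rule gives 220.

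**Step 2. Test each target against the over-recruitment rule.**
- 222: (222 − 202)/202 = 9.9%, which is 10% after rounding to a whole, even number.
- 220: (220 − 202)/202 = 8.9%, which is short of 10%.

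**Step 3. Test each target against a 10% loss of those recruited.** Analysable number = target × (1 − 0.10).
- 222 × 0.90 = 199.8, which is 2.2 below 202.
- 220 × 0.90 = 198, which is 4 below 202.

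**Step 4. Find the loss each target tolerates.** Largest loss that still leaves 202 = 1 − 202/target.
- 222: 1 − 202/222 = 9.0%.
- 220: 1 − 202/220 = 8.2%.

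| Target | Above 202 | Left after 10% loss | Loss tolerated |
|---|---|---|---|
| 222 | 9.9% | 199.8 | 9.0% |
| 220 | 8.9% | 198 | 8.2% |

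For comparison, absorbing a full 10% loss would need 202/0.90 = 224.4, so 225, or 226 with equal arms.

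**Step 5. Size of the effect.** The standard error of the treatment difference varies with 1/√n. With 199.8 instead of 202 it grows by a factor √(202/199.8) = 1.005; with 198 the factor is √(202/198) = 1.010. That is about 0.5% and 1%.

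Power needs assumptions. Three sets that reproduce 101 per group with a margin of 3.5 and no true difference are shown below. They are illustrations, not the plan's inputs.

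| Assumed alpha (one-sided) | Assumed SD | Power at 202 | At 199.8 | At 198 |
|---|---|---|---|---|
| 5% | 10 | 80.0% | 79.6% | 79.3% |
| 2.5% | 8.88 | 80.0% | 79.6% | 79.2% |
| 2.5% | 7.67 | 90.0% | 89.7% | 89.4% |

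The loss of power is below one percentage point in every case.

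**The case against.** The strongest defence is that 222 is not a mistake. Statistical methods {20a} defines the allowance as 10% on top of the power calculation, and 222 is exactly that. Sample size {14} speaks of a margin and does not state that 10% of children are expected to be lost. This stands. A reader might infer that 222 is an arithmetic error and that the protocol was bound to divide by 0.90 and reach 225 or 226. The document does not support that, because it never commits to that inflation. What remains against 222 is narrow: the wording in {14} ties the 10% to loss to follow-up, and read as a proportion lost, 222 does not quite cover it.

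The defence does not reach 220, which fails on either reading. It may be a rounded figure in the Abstract, but it recurs in the sections on randomisation and on how far recruitment may run.

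It is also fair to say that 202 is itself introduced as an initial calculation, that retention measures are planned, and that multiple imputation and sensitivity analyses are named for missing data. No conclusion is likely to turn on 198 or 200 children rather than 202. That limits the weight of the point but does not remove the contradiction.

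A reader might further infer that two targets leave the block list undefined. This is weak. Randomisation is stratified by Gartland type, and the number in each stratum is not known in advance, so the lists could not be cut to an exact total in any case. Blocking within strata keeps the arms balanced whichever target applies.

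**Conclusion.** The point holds as an inconsistency with a small numerical consequence. The target is 222 in one section and 220 in three, and 220 satisfies neither the 10% over-recruitment rule nor a 10% loss. The figure 222 satisfies the over-recruitment rule and tolerates 9.0% loss, so the description in Sample size {14} is slightly generous.

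At 10% loss the shortfall against 202 is about 2 children with 222 and 4 with 220. These figures rest only on numbers in the protocol and on reading the 10% in {14} as the proportion of recruited children lost.

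A reader might go further and conclude that the trial is underpowered. The figures do not support that: the standard error grows by about 1% at most, and power falls by less than one point under each assumption tried. The exact effect on power cannot be stated, because the SD, alpha and power are not given.

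**What to change.** Use 222 as the single target in the Abstract, Sample size {14}, Sequence generation {16a} and Interim analyses {21b}. In Sample size {14}, describe it as 10% over-recruitment above 202, which tolerates about 9% loss to follow-up. Statistical methods {20a} can then stay as it is.

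If the sponsor prefers 220, state that it tolerates about 8% loss, and amend {20a}, since 220 is about 9% and not 10% above 202.

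The first option costs wording and two more children than 220 (222 − 220 = 2). Recruitment {15} reports available cases 50% above the required number, so those two are not an obstacle. An increase to 225 or 226 is needed only if the sponsor does mean to absorb a 10% loss of those recruited.
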